### 3.1. Outcome Definitions and Scoring Direction

All outcomes will be assessed at baseline (T0) and after the conclusion of the four-month intervention period (T1). For each outcome, change scores will be calculated as the post-intervention score minus the baseline score (T1 − T0). The direction of clinical interpretation depends on the scoring system of each instrument.

For the primary outcome, a positive change in the Montreal Cognitive Assessment (MoCA) total score will indicate improvement in objective global cognitive performance.

While the MoCA is a screening instrument, its designation as the primary endpoint is clinically justified by its widespread validation, brief administration time (minimizing evaluation fatigue in active cancer patients), and extensive use as a benchmark across CRCI trials, allowing for direct cross-study comparisons. Furthermore, the MoCA exhibits superior sensitivity to the specific neurocognitive phenotypes of “chemobrain” compared to other global screeners, as it incorporates rigorous subtests dedicated to executive functions, working memory, sustained attention, and delayed verbal recall. To actively mitigate the inherent risk of Type II errors and address potential ceiling effects in this relatively young and functional patient population, the MoCA is structurally supplemented within this multi-method protocol by robust secondary measures capable of capturing subtle cognitive fluctuations.

For FACT-Cog, higher scores indicate enhanced cognitive functioning and elevated cognitive-related quality of life. For the PECC and the Lawton and Brody Scale, higher scores are indicative of better every day cognitive performance and greater functional autonomy, respectively. Conversely, higher scores on the Hamilton Anxiety Scale, Pittsburgh Sleep Quality Index, ECOG Performance Status Scale, and Everyday Life Memory Failures Questionnaire will indicate worse anxiety symptoms, poorer sleep quality, poorer functional performance status, and more frequent everyday memory failures, respectively.

The primary endpoint will be the between-group difference in change in MoCA total score from T0 to T1. The primary comparison will be between the ALMA group intervention (G2) and the health education control group (G0). Secondary comparisons will include G2 versus G1. The G1 versus G0 comparison, if reported, will be interpreted as exploratory.

### 3.2. Primary Outcome: Objective Global Cognitive Performance

The primary endpoint will be the between-group difference in change in MoCA total score from baseline (T0) to post-intervention assessment (T1), calculated as ΔMoCA = MoCA score at T1 − MoCA score at T0. The MoCA is a brief standardized cognitive screening instrument that evaluates multiple cognitive domains, including executive functions, attention, abstraction, memory, calculation, language, visuospatial abilities, and orientation. The total score ranges from 0 to 30, with an administration time of approximately 10–12 min. To correct for socio demographic educational bias, an additional point is added to the total score for participants with ≤12 years of formal education. The Spanish version exhibits robust psychometric validity, with a reported internal consistency of Cronbach’s α = 0.84 and a test–retest reliability of r = 0.92. A score below the clinical cut-off of <26 points indicates objective cognitive impairment. For cancer-related cognitive impairment (CRCI) monitoring, the Minimal Detectable Change (MDC) is established at ±2 points; thus, an intra-subject post-intervention increase of ≥2 points indicates a true, statistically stable cognitive improvement.

In this study, the MoCA will be used as an objective global measure of cognitive functioning rather than as a diagnostic tool for cancer-related cognitive impairment [30].

Although CRCI may involve subtle and domain-specific cognitive changes, the MoCA was selected as the primary outcome because it provides a standardized, feasible, and clinically interpretable measure of global cognitive performance. To complement this global measure, secondary outcomes will include patient-reported cognitive functioning, everyday cognition, functional autonomy, sleep quality, anxiety, performance status, and everyday memory failures.

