### 2.4. Sample Size

The planned sample size for this trial is 63 women with breast cancer undergoing active oncological treatment, with 21 participants allocated to each of the three study arms: health education control group (G0), individual cognitive training group (G1), and ALMA group intervention (G2).

The sample size calculation was based on the primary outcome, defined as the change in objective global cognitive performance from baseline (T0) to post-intervention (T1), assessed using the Montreal Cognitive Assessment (MoCA). As no directly comparable previous trial evaluating the ALMA intervention in women with breast cancer was available, the expected effect was estimated using an indirect reference study that evaluated a multicomponent cognitive stimulation programme and reported a mean post-intervention increase of 2.95 points in MoCA score [27]. Assuming a common standard deviation of 3.48, this corresponded to an estimated standardized effect size of Cohen’s d ≈ 0.85.

For the purposes of sample size estimation, this effect was converted to an approximate ANOVA effect size of f ≈ 0.40. The calculation was performed using G*Power software, version 3.1.9.7 [28], for a balanced one-way fixed-effects ANOVA with three independent groups, an alpha level of 0.05, statistical power of 80%, and equal allocation across groups. Under these assumptions, a minimum total sample of 57 participants was required to detect an overall between-group difference.

To account for an anticipated attrition rate of approximately 10%, the recruitment target was increased to 63 participants, corresponding to 21 participants per study arm. This inflation is intended to preserve statistical power for the primary analysis under the intention-to-treat principle.

Although the primary effectiveness analysis will be conducted using linear mixed models to evaluate the Group × Time interaction across baseline and post-intervention assessments, the ANOVA-based sample size calculation was used as a conservative and transparent approximation for planning purposes. Linear mixed models are expected to make efficient use of repeated-measures data and to accommodate missing outcome data under the missing-at-random assumption. Therefore, the ANOVA-based calculation was considered appropriate for estimating the minimum feasible sample size while maintaining consistency with the planned three-arm randomized design.

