The planned between-group comparisons for the primary outcome will focus on the ALMA group intervention (G2). The first planned comparison will evaluate the difference in change in MoCA total score from T0 to T1 between G2 and the health education control group (G0). The second planned comparison will evaluate the difference in change in MoCA total score from T0 to T1 between G2 and the individual cognitive training group (G1), in order to assess the potential added value of the multidimensional group-based ALMA intervention over individual cognitive training. The comparison between G1 and G0 will not be considered a planned efficacy comparison and, if reported, will be interpreted as exploratory.

To strictly prevent statistical overfitting and safeguard the degrees of freedom given the target sample size of 21 participants per study arm, the adjusted model will be parsimoniously restricted. Specifically, a maximum of two pre-specified baseline covariates will be simultaneously controlled for as fixed effects: chronological age (in years) and educational level (in years of formal schooling). Baseline cognitive stratification variables will be excluded from the model as covariates, given that their equilibrium across groups is already mathematically guaranteed by the stratified block randomization procedure (Section 2.5). Additional clinical and psychological variables including disease stage, treatment modality, time since diagnosis, cancer-related fatigue/performance status, baseline anxiety symptoms (Hamilton Anxiety Scale), and baseline ECOG Performance Status will be exclusively examined in exploratory or sensitivity analyses rather than included simultaneously in the primary adjusted model.

Because two planned comparisons will be conducted for the primary outcome, namely G2 versus G0 and G2 versus G1, Holm–Bonferroni correction will be applied to these two comparisons to control the family-wise error rate. Holm–Bonferroni correction will also be applied to secondary outcome comparisons within each outcome family when appropriate. Any additional post hoc analyses, including G1 versus G0 comparisons, will be clearly labelled as exploratory.

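### The education point cancels out of the MoCA change score and, if the total is held to 0–30, takes one point of gain from less-schooled women who reach the ceiling: a minor, avoidable bias towards no effect

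*Protocol article*

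**What the plan says.** All three elements stand in section 3.2 (Primary Outcome):

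- The scale: "The total score ranges from 0 to 30".
- The correction, meant to offset educational bias: "an additional point is added to the total score for participants with ≤12 years of formal education".
- The endpoint: "calculated as ΔMoCA = MoCA score at T1 − MoCA score at T0".

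The section does not say whether the corrected total is held at 30, or whether the change uses the raw or the corrected total. It also treats an individual rise of at least 2 points as true improvement.

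Elsewhere, section 2.5 stratifies at MoCA <26 versus ≥26, and Table 2 sets no upper MoCA limit, so high scorers enter the trial. Section 3.9 restricts the adjusted model to two covariates, "chronological age (in years) and educational level (in years of formal schooling"). Sections 3.1 and 6 acknowledge that the MoCA may have a ceiling effect, but neither mentions the education point.

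**The concern.** The correction makes sense when a single score is compared with a cut-off. The primary endpoint is a within-woman change, and there the correction has no work to do: the same point is added at T0 and T1. Its only possible effect is at the top of the scale. With the stated maximum of 30, it lowers the usable ceiling by one raw point for women with ≤12 years of schooling. More women reach the ceiling at T1 in an arm that improves, so the effect is not neutral between arms. At stake is a small shrinkage of the G2–G0 and G2–G1 differences, in a trial with 21 women per arm that already concedes a type II risk for this instrument.

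**Working it through.** **Inputs from the documents.** Section 2.4: the reference study "reported a mean post-intervention increase of 2.95 points in MoCA score"; "Assuming a common standard deviation of 3.48". These reproduce the plan's standardized effect: 2.95 / 3.48 = 0.848, or about 0.85. Section 3.2: range 0–30, test–retest r = 0.92.

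**Assumptions, not in the documents.** Mean raw MoCA at T0 of 24–26; 30–70% of women with ≤12 years of schooling; no gain in G0; r = 0.60 as an alternative.

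**Step 1: case arithmetic.** For a woman with ≤12 years of schooling, the capped score is min(raw + 1, 30).

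| Raw T0→T1 | Raw change | Uncapped | Capped | Capped change |
|---|---|---|---|---|
| 24→27 | +3 | 25→28 | 25→28 | +3 |
| 29→30 | +1 | 30→31 | 30→30 | 0 |
| 28→30 | +2 | 29→31 | 29→30 | +1 |
| 27→30 | +3 | 28→31 | 28→30 | +2 |
| 30→30 | 0 | 31→31 | 30→30 | 0 |
| 30→28 | −2 | 31→29 | 30→29 | −1 |

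Without a cap the change is always right, although some scores are 31. With a cap, the change is altered only when raw 30 occurs at exactly one visit. In the 28→30 row, a woman who meets the protocol's own 2-point criterion is scored as missing it.

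**Step 2: effect on the group difference.** Simulation: true score ~ N(mean, 3.48² × 0.92), error variance 3.48² × 0.08 at each visit, scores rounded and limited to 0–30, gain 2.95 in G2. The raw change is compared with the capped change.

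- Central case (mean 25, 50% with ≤12 years): G2–G0 is 2.47 raw and 2.36 capped. The loss is 0.115 (4.6%).
- Over the assumed ranges: loss 0.052–0.196 points (2.0–8.7%). The change is altered in 5–20% of G2 and 1–5% of G0. In an arm of 21, the G2 figure is about 1 to 4 women (0.05 × 21 = 1.05; 0.20 × 21 = 4.2).
- With r = 0.60 the loss in points is almost the same.
- With a gain of 1.5 the shrinkage is about 1.5–7%.

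**Step 3: comparison with the natural ceiling.** The 0–30 limit alone cuts the true 2.95 to 2.47 at mean 25 (a cost of 0.48) and to 2.24 at mean 26 (0.71). With 50% at ≤12 years, the education cap adds 0.115 and 0.14.

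**Step 4: power for G2–G0** (two-sided t-test, 19 per arm, alpha 0.05, gain 2.95).

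- r = 0.92: 0.995–1.000 raw, 0.987–1.000 capped; the loss is under 1 percentage point.
- r = 0.60: a loss of about 1–5 points.
- SD of change set to 3.48, mean 26, 50% with ≤12 years: 0.490 falls to 0.442, about 5 points.

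The protocol does not say whether 3.48 is an SD of scores or of changes, so these cases are kept apart.

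**The case against.** The strongest reply is that this is a scoring detail. The article condenses a fuller plan and names a versioned instrument (MoCA v8.3, Table 3), so the cap and the choice of total may be settled in a scoring manual or analysis plan that is not shown. Section 3.1 also values comparison with other studies, which favours the corrected total. Both points limit the weight of the finding. Neither gives the education point a use in a change score, and comparability can be served by a descriptive table.

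Several stronger readings are tempting but not supported:

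- *Every woman with ≤12 years of schooling is mis-scored.* No. With raw scores of 29 or less at both visits the point cancels exactly. Among such women in G2, about 65–92% are unaffected for baseline means of 22–27.
- *A score of 31 biases the endpoint.* No. It contradicts the stated range but leaves the change intact. The bias needs a cap, which is inferred from that range and not stated.
- *The data checks would catch a 31.* Section 3.7.2 plans range checks where possible and gives no MoCA limits.
- *Effects in less-educated women will be misreported.* No analysis by education subgroup is planned.

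In the other direction, the schooling covariate in section 3.9 is no remedy: it cannot restore a point that has been truncated.

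**Conclusion.** The point holds as a minor one. In the primary endpoint the education point has no corrective effect. If totals are held to the stated range, it removes one point from women with ≤12 years of schooling who rise to raw 30, and it hides one point of decline in those who fall from 30. The net effect on G2–G0 is a bias towards zero of about 0.05–0.20 points (2–9%) at a gain of 2.95. The direction is the same for G2–G1 as long as ALMA gains more; its size was not computed, because the protocol gives no expected gain for G1. The size depends on the assumed baseline mean and education mix. The bias is generally smaller than the natural ceiling already disclosed in section 6, and it would not decide the trial. It is worth removing because it is avoidable.

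**What to change.** In section 3.2, define ΔMoCA and the mixed-model outcome on the raw 0–30 total, without the education point. State that the education-corrected total, capped at 30, is used only for the <26/≥26 stratification in section 2.5 and for descriptive classification. This also settles which total defines the stratum: a raw 25 with ≤12 years of schooling becomes 26 and changes stratum.

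The cost is a sentence or two in the protocol and the analysis plan, and no new assessment. The database should hold the raw total, because a capped 30 in a woman with ≤12 years of schooling could be raw 29 or raw 30. The analysed means will be slightly lower than education-corrected means in other studies, so corrected means by arm and visit can be tabulated alongside. The natural ceiling remains.

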### 3.3. Secondary Outcomes

Secondary outcomes will include subjective cognitive function, everyday cognition, functional autonomy, anxiety, sleep quality, performance status, and everyday memory failures.

Functional Assessment of Cancer Therapy-Cognition (FACT-Cog), Version 3: To assess patient’s perceived cognitive functioning and its impact on quality of life. The FACT-Cog assessment is composed of 37 item questionnaires, which are divided into six cognitive domains: memory, concentration, mental acuity, verbal fluency, functional interference, and multitasking ability. The scale is composed of three subscales: symptoms of perceived cognitive impairment, where a higher score indicates fewer symptoms; perceived cognitive abilities, where a higher score indicates superior cognitive skills rating; and overall quality of life, where a higher score indicates an enhanced quality of life relative to cognition [31]. Validated in Spanish oncology cohorts, it demonstrates exceptional internal consistency α = 0.93 for the global scale α = 0.90 for the CogPCI subscale) and a test–retest reliability coefficient of r = 0.84. Higher total or subscale scores indicate fewer subjective cognitive complaints and a higher cognitive-related quality of life. The MCID for the total score ranges between 6.9 and 10.6 points (and 4.6 points specifically for the CogPCI subscale) to establish a clinically meaningful therapeutic improvement.The Test for the Assessment of Everyday Cognition (PECC) is a standardized instrument designed to evaluate an individual’s capacity to manage day-to-day activities. The PECC assesses an individual’s ability to solve 12 real-life scenarios, which are grouped into the following domains: medication, administrative management, financial management, food preparation, transportation, and shopping. The PECC provides a comprehensive assessment of an individual’s functional capacity in daily living activities, thereby providing valuable insights into their overall cognitive abilities and daily living skills. The administration time is 35 min [32]. Normatively validated in Spain for adult populations, the PECC demonstrates an excellent inter-rater reliability with an Intraclass Correlation Coefficient (ICC) of 0.94, alongside robust ecological validity. Scores are calculated continuously per domain and then aggregated, where higher cumulative scores denote superior objective functional autonomy. A statistically significant post-intervention increase relative to the control group demonstrates successful clinical transfer of trained cognitive strategies to the patient’s actual environment.The Lawton and Brody Scale is a tool designed to evaluate autonomy in instrumental activities of daily living. The administration time for this assessment is four minutes. It measures 8 semi-complex tasks: telephone use, shopping, food preparation, housekeeping, laundry, mode of transportation, responsibility for own medications, and financial management. Each item is scored binary as either 0 (dependent) or 1 (independent), yielding a total score from 0 to 8 in women [33]. It exhibits high cross-cultural reproducibility with a Guttman scalogram coefficient of 0.96. A total score of 8 indicates complete functional independence. Any score <8 establishes functional decline. Therapeutic success is operationalized as the preservation of maximum baseline autonomy (score of 8) or a reduction of dependency indicators post-chemotherapy.The Hamilton Anxiety Scale is a psychometric instrument that is employed to evaluate the severity of anxiety in patients who meet criteria for anxiety [34]. The scale consists of 14 items, each with five response options ranging from “not present” to “very severe” with a total score range of 0 to 56. The adapted Spanish version demonstrates high internal consistency (α = 0.89) and inter-rater reliability (r = 0.94). Clinical severity thresholds are categorized as: ≤17 (mild anxiety), 18–24 (mild-to-moderate anxiety), and 25–30 (moderate-to-severe anxiety). The MDC for this instrument is 4 points; thus, a post-intervention decrease of ≥4 points confirms a statistically reliable and clinically significant therapeutic reduction in anxiety.The Pittsburgh Sleep Quality Index (PSQI) was developed to assess sleep quality in individuals between the ages of 24 and 83. This instrument requires approximately 5 to 10 min for completion. The study’s objective is to assess the impact of subjective sleep quality, sleep latency, sleep duration, habitual sleep efficiency, sleep disturbances, sleep medication use, and daytime dysfunction on a total of 19 individual items [35]. Validated in Spanish oncology settings, it displays an internal consistency of α= 0.81 and high diagnostic sensitivity (89.6%). A global score >5 serves as the clinical cut-off point, separating “good sleepers” from “poor sleepers” (chronic sleep pathology). The MDC is 2 points, meaning a downward shift of ≥2 points post-intervention establishes a clinically relevant improvement in sleep hygiene.The Performance Status Scale (ECOG): Is a standardized scale used to evaluate the functional status of cancer patients and assess their ability to perform activities of daily living. It allows for an assessment of the disease’s impact on the patient’s functional status and helps guide therapeutic and prognostic decisions. The scale classifies functional status on a scale of 0 to 5. The numeral 0 indicates Patient is fully active, with no restrictions on performing daily activities;1: Limited ability to perform physically strenuous activities, but capable of light or sedentary work; 2: Capable of self-care, though unable to perform work activities; remains active more than 50% of the day; 3: Limited capacity for self-care; remains in bed or a chair more than 50% of the day; 4: Completely disabled; totally dependent for self-care; 5: Death. This scale ensures tight control over confounding physical decline during the trial; maintaining a Grade 0 or 1 throughout the study indicates clinical stability. [36].The Everyday Life Memory Failures (MFE) Questionnaire is a tool designed to assess various forms of memory impairment, a 28 item self-report instrument designed to evaluate the subjective frequency of cognitive lapses and minor memory failures occurring within the patient’s typical daily environment. Respondents rate each item on a 5-point Likert scale (0 = never to 4 = very often), with total scores ranging from 0 to 112. It encompasses a range of categories, including verbal memory, reading aptitude, writing skills, recognition of names, faces, and actions, as well as the ability to learn new information. The response to this question is measured using a Likert scale, which provides nine possible responses ranging from “Not once in the last 3 months” to “More than 1 time a day” [37]. The Spanish version exhibits a robust internal consistency (α= 0.89) and a stable test–retest reliability (r = 0.83). Higher cumulative scores reflect a higher density of daily cognitive failures, with normative healthy adult data averaging scores of 20–25. Consequently, a downward change score (Δ MFE < 0) post-intervention demonstrates an increase in perceived daily cognitive control and efficiency.

### 3.4. Clinical and Sociodemographic Variables

In addition to the outcomes above, the analysis will incorporate:

Sociodemographic data: Age, level of education, and marital status.

Clinical profile: Type of oncological treatment (chemotherapy, radiotherapy, hormone therapy), time since diagnosis, and general health status.

### 3.5. Blinding and Allocation Concealment

Due to the nature of the ALMA cognitive intervention, complete blinding of the participants and the therapists delivering the sessions is not possible. Furthermore, assigning an independent assessor for the post-intervention evaluations (T1) is unfeasible due to human resource constraints within the specialized clinical setting and the strict methodological requirement to minimize inter-rater variability during manual neuropsychological testing. To mitigate potential detection bias and safeguard internal validity, several countermeasures have been adopted. First, all primary and secondary outcome measures including the Montreal Cognitive Assessment (MoCA) and the Test for the Assessment of Everyday Cognition (PECC) utilize standardized, highly structured, and objective quantitative scoring systems that eliminate subjective interpretation. Second, manual tests will be supplemented by objective, computerized automated scoring software where applicable to ensure absolute data consistency. Finally, the statistical analysis will be performed by an external biostatistician who will remain completely blinded to group allocation, working exclusively with anonymized datasets.

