Non-blinded investigator: A notable methodological constraint of this protocol pertains to the absence of a blinded evaluator for the neuropsychological tests. This is due to the fact that the same professional responsible for the initial and final assessments is also the one who conducts the ALMA group interventions. This arrangement, motivated by resource optimization and the need to maintain a consistent therapeutic relationship with the participants, could introduce detection bias or researcher expectations bias in the administration of the post-intervention instruments. Nevertheless, a range of strategies will be implemented to mitigate this risk and safeguard the integrity of the findings. These include standardizing assessment instruments, implementing statistical analysis without the researcher’s knowledge, ensuring that participants are unaware of the hypothesis, and utilizing robust modeling (LMM).

Additionally, to prevent subconscious cueing or expectancy effects during post-intervention (T1) evaluations, a rigid behavioral protocol will be enforced. This includes the strict use of manualized verbatim scripts for all test administrations to ensure identical phrasing, the systematic maintenance of a neutral affective posture (suppressing non-verbal reinforcements such as nodding or smiling, and avoiding differential verbal praise), and the use of precise digital timers to govern all response windows objectively, thereby completely eliminating investigator discretion.

Attrition Risk: The nature of the population (patients in active oncological treatment) poses a risk of dropout due to medical complications, fluctuating health status, or scheduling conflicts. While retention strategies are in place, high attrition could impact the statistical power of the final analysis.

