### 7.3. Informed Consent and Safety

Written informed consent will be obtained from all participants before any study-related procedure is conducted. Participants will receive an information sheet describing the objectives of the study, study procedures, randomization process, potential risks and benefits, confidentiality measures, voluntary nature of participation, and right to withdraw at any time without consequences for their usual oncological care. The model informed consent form and participant information sheet will be available in Supplementary Material S3 and retained in the study documentation according to the requirements of the Research Ethics Committee.

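### The objective-scoring safeguard offered for the unblinded assessor can cover at most two of the eight outcomes; the other six, all secondary, are self-reports or ratings

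*Protocol article*

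**What the plan says.** Section 3.5 states that participants and therapists cannot be fully blinded and that an independent T1 assessor is not feasible. It then lists countermeasures. The first covers "all primary and secondary outcome measures including the Montreal Cognitive Assessment (MoCA" and also names PECC; these measures are said to "utilize standardized, highly structured, and objective quantitative scoring systems that eliminate subjective interpretation".

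Section 6 acknowledges that "the same professional responsible for the initial and final assessments is also the one who conducts the ALMA group interventions", and Section 2.11 assigns both tasks to the principal researcher. Among the mitigations in Section 6 is "ensuring that participants are unaware of the hypothesis". Section 6 adds verbatim scripts, a neutral manner and digital timers at T1.

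Section 7.3 says of consent: "Participants will receive an information sheet describing the objectives of the study, study procedures, randomization process, potential risks and benefits". Section 2.2 likewise has the objectives and procedures explained at the first consultation.

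Section 3.3 lists the secondary measures: "Secondary outcomes will include subjective cognitive function, everyday cognition, functional autonomy, anxiety, sleep quality, performance status, and everyday memory failures". The stated purpose of FACT-Cog is "To assess patient’s perceived cognitive functioning and its impact on quality of life", and the MFE is a self-report "designed to evaluate the subjective frequency of cognitive lapses and minor memory failures".

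**The concern.** Section 3.5 uses the nature of the scoring to justify having the ALMA therapist assess outcomes. If the scoring does not have that property, the justification fails for the outcomes concerned, and a reader of the eventual report would credit them with protection they never had.

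The setting makes this relevant. A woman in G2 may spend 32 × 120 min = 3,840 min = 64 hours with the person who later administers her T1 assessment. G0 has no contact between assessments (Section 2.6.1). ALMA tasks are built mainly around each woman's own complaints (Section 2.6.3), which is close to what FACT-Cog and MFE measure. Expectancy or a wish to please could move these outcomes toward ALMA in both planned comparisons.

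The secondary scales also carry interpretive weight. Section 3.3 treats a fall of at least 4 points on Hamilton, or at least 2 on PSQI, as a real clinical improvement. Section 6 relies on FACT-Cog, together with PECC, to offset the limits of MoCA.

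**Working it through.** No planned figure is in dispute, so the check is a classification of the eight outcomes in Table 3 against their descriptions in Sections 3.2 and 3.3 and in Table 1.

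| Outcome | How the article describes it | Type |
|---|---|---|
| MoCA (primary) | standardized cognitive test, 0–30 | performance test |
| PECC | solving 12 real-life scenarios; inter-rater ICC 0.94 | performance test |
| FACT-Cog | perceived cognitive functioning | self-report |
| MFE | 28 self-report items on frequency of lapses | self-report |
| PSQI | includes subjective sleep quality | self-report |
| Hamilton | 14 items graded for severity; inter-rater r = 0.94 | rating |
| Lawton and Brody | 8 activities, each dependent or independent | rating or reported function |
| ECOG | grade 0 to 5 of functional status | rating |

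Count: 2 performance tests + 3 self-reports + 3 ratings = 8. The universal statement fails for 3 + 3 = 6 of 8 outcomes, which is 6 of the 7 secondary outcomes. Table 1 draws part of the same line, placing PECC and MoCA under objective cognition and FACT-Cog and MFE under subjective cognition.

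Even for PECC the claim is too absolute, since an inter-rater ICC of 0.94 leaves some rater variation. Section 3.5 itself gives the need to limit inter-rater variability as a reason for keeping a single assessor. That reason would have little force if scoring removed all interpretation.

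Next, do the other safeguards reach the six?

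- Scripts, neutral manner and timers (Section 6) standardize how tests are given. They do not alter a woman's view of her own memory or sleep, and they do not settle a severity grade.
- The blinded biostatistician (Section 3.5) works on data already recorded.
- Unawareness of the hypothesis (Section 6) would reach them if it held. Set beside Sections 2.2 and 7.3, women are told the objectives, the procedures, the randomization process and the potential benefits. The primary objective in Section 1 names ALMA, the improvement sought and both comparators. The article describes no step that keeps the hypothesis from them.

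Illustration only: the bias sizes are assumptions and appear nowhere in the documents. Take a two-arm comparison of mean change with no true effect, n per arm, and a pure bias of b SD of change favouring ALMA. The chance of a significant result at two-sided 0.05 follows from the noncentral t with 2n − 2 degrees of freedom and noncentrality b × √(n/2).

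| b (assumed) | n = 21 (randomized) | n = 19 (57/3) |
|---|---|---|
| 0.2 | 0.2 × √10.5 = 0.65, about 10% | 0.2 × √9.5 = 0.62, about 9% |
| 0.3 | 0.97, about 16% | 0.92, about 15% |
| 0.5 | 1.62, about 35% | 1.54, about 32% |

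These use an unadjusted 0.05. Holm correction, planned for secondary comparisons when appropriate (Section 3.9), would lower them.

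**The case against.** The strongest reply is that Section 3.5 calls the *scoring systems* objective, not the outcomes, and that the article labels FACT-Cog and MFE as subjective elsewhere, so nobody is misled about what they are. This is partly right. Fixed scoring arithmetic is objective in a narrow sense, but it does not remove the respondent's or rater's judgement. The sentence is offered as protection against detection bias for all measures, and there it is wrong.

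Several stronger readings are tempting, and the documents do not support them.

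- *That the article hides the lack of blinding or the unequal contact.* It does not. Section 2.5 calls the trial open-label, Section 6 names detection and expectation bias, and Sections 4.1 and 6 discuss differential contact.
- *That Section 6 claims to remove investigator discretion for the self-reports.* That phrase is attached to scripts, manner and timers during test administration.
- *That consent demonstrably discloses the directional hypothesis.* Being told the objectives is in tension with being unaware of the hypothesis but does not prove disclosure. The information sheet is in Supplementary Material S3, which is not shown.
- *That women give their questionnaire answers aloud to the therapist.* The article says the principal researcher administers assessments; how FACT-Cog, MFE and PSQI are completed is not stated.
- *That the bias can be scaled against the effect in the sample-size section.* That effect is for MoCA and is no yardstick for the other outcomes.

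There are also existing protections against over-reading. MoCA is the sole primary outcome, and Section 3.9 requires subjective memory failures to be read alongside it. That rule is not stated for FACT-Cog, PSQI or Hamilton.

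**Conclusion.** The point holds as a correction to an overstated mitigation. The claimed property is absent for six of eight outcomes, all secondary, and is too absolute even for PECC. The count rests on the article's own descriptions. It does not say who completes ECOG or Lawton and Brody, but either way these are judgements or reported function and not performance tests. The hypothesis statement in Section 6 and the consent content in Sections 2.2 and 7.3 must be reconciled; whether they truly conflict depends on an information sheet not shown.

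The size of any resulting bias is unknown, and the percentages above show only how assumed shifts would behave at this sample size. The misstatement does not bear directly on MoCA, whose exposure to an unblinded assessor is already disclosed. The consequence is for how the secondary results are protected and interpreted, which makes this worth changing but not critical.

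**What to change.** 1. In Section 3.5, limit the objective-scoring statement to MoCA and PECC and drop the verb *eliminate*. State that FACT-Cog, MFE, PSQI, Hamilton, ECOG and Lawton and Brody are open to reporting or detection bias.
2. In Section 6, either justify the statement about the hypothesis, by saying what the information sheet tells women and what it withholds, or remove it.
3. Have women complete FACT-Cog, MFE and PSQI themselves, in private, on paper or by electronic survey, before any contact with the therapist at T1. Use the same mode at T0 so that change scores do not mix modes.
4. In Section 3.9, extend the rule for subjective memory failures to FACT-Cog, PSQI and Hamilton, and state that none of these can by itself support a claim of cognitive benefit if MoCA is null.

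Cost: items 1, 2 and 4 are wording. Item 3 is a new but inexpensive step. Section 3.7.1 plans REDCap or an equivalent for data capture with access restricted to the research team, so participant entry is not already planned and would need set-up or paper forms. The downside is slightly more item-level missing data. No added assessor or visit is needed.
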